#### 4.3.1 Cervical HPV infections

- **Incident cervical HPV infection:** an incident cervical infection with a given HPV type is defined as the new detection of this HPV type (by PCR) at any time point during the follow-up period (i.e. after enrolment in the control arm of study HPV-008).
- **Transient cervical HPV infection:** a transient cervical infection with a given HPV type is defined as the detection of this HPV type (by PCR) at any single time point during the follow-up period followed by a negative sample for that HPV type at the evaluation performed 6 months after the evaluation when the cervical HPV infection was first detected.
- **6-month persistent cervical HPV infection:** a persistent cervical HPV infection (6-month definition) is defined as the detection of the same HPV type (by PCR) in cervical samples at two consecutive evaluations over approximately a 6-month interval. Thus, the algorithmic definition of a 6-month persistent infection is that there exists a sequence of positive samples with the same HPV type, not interrupted by negative samples, such that the total range is more than 5 months ( $> 150$  days). The start of the persistent cervical HPV infection is defined as the date of the first positive sample in the sequence.
- **12-month persistent cervical HPV infection:** a persistent cervical HPV infection (12-month definition) is defined as the detection of the same HPV type (by PCR) at all available time points over approximately a 12-month interval. Thus, the algorithmic definition of a 12-month persistent cervical infection is that there exists a sequence of positive samples with the same HPV type, not interrupted by negative samples, such that the total range is more than 10 months ( $> 300$  days). The start of the persistent cervical HPV infection is defined as the date of the first positive sample in the sequence.
- **Other cervical HPV infection:** other cervical HPV infections than those described above will be considered in the analysis. These infections are cervical HPV infections with duration less than 150 days and cervical HPV infections detected at the last visit and for which it is not possible to determine if they are transient or persistent.

- **Clearance of cervical HPV infection:** two definitions will be used:

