### **6.2.7 Analysis of time to first detected cervical HPV infections**

#### **6.2.7.1 Population**

The population for the analysis of time between the start of sexual activity and a first detected incident cervical HPV infection (or a first confirmed 6-month cervical HPV infection) will be restricted to subjects from the TVC-1-Control arm cohort for whom the date of start of sexual activity is known (i.e. either collected or computed, so that a starting date is available for the computation of the time between the start of sexual activity and a first detected cervical HPV infection) and for whom the date of start of sexual activity is either less than 6 months prior to their inclusion in the study or during the follow-up period.

Subjects with cervical HPV infections preceding the start of sexual activity will not be taken into account in the analyses.

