### 6.2.7.3 Event variable

The analyzed event - first incident cervical HPV infection (or a first confirmed 6-month cervical HPV infection) - will be analyzed by means of a binary variable with the following categories:

- 1 = First detected cervical infection following the start of sexual activity
- 0 = No detection of cervical HPV infection following the start of sexual activity

The event will be determined as showed with the following examples (See section 8.4.3 for more details):

| Sub-
ject* | Detected cervical HPV infections**
over the follow-up period
(in chronological order)                                                                                                                   | Subject
included
in analysis
population | Event
(first
infection)
(0 = No /
1 = Yes) | Event
(first
persistent)
(0 = No /
1 = Yes) |
|---------------|---------------------------------------------------------------------------------------------------------------------------------------------------------------------------------------------------------------|--------------------------------------------------|--------------------------------------------------------|---------------------------------------------------------|
| A             | -                                                                                                                                                                                                             | Yes                                              | 0                                                      | 0                                                       |
| B             | Transient infection associated with HPV type X
Transient infection associated with HPV type Y                                                                                                              | Yes                                              | 1                                                      | 0                                                       |
| C             | Transient infection associated with HPV type X
Transient infection associated with HPV type Y
12-month persistent infection associated with HPV type Y                                                  | Yes                                              | 1                                                      | 1                                                       |

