### 6.2.7.4 Time computation

The time to a first detected incident cervical HPV infection (or a first confirmed 6-month cervical HPV infection) following the start of sexual activity will be calculated in days as: Date of event or Date of censoring - Date of start of sexual activity.

The date of start of sexual activity will be determined as follows:

- For subjects who already had sexual intercourse prior to study entry: the date of start of sexual activity will correspond to the birthdate collected in the CRF plus the age at first sexual intercourse collected in the baseline behavioral questionnaire,.
- For subjects who did not have sexual intercourse prior to study entry: the date of start of sexual activity will correspond to the maximum between i) the date of the yearly questionnaire in which subjects reported having first sexual intercourse (or the date of the visit corresponding to the yearly questionnaire if the date of the questionnaire is missing) and ii) the date of the preceding detected cervical HPV infection, minus the date of the preceding questionnaire (or visit), divided by 2. In case there is no preceding questionnaire (i.e. baseline questionnaire is missing and first sexual intercourse is reported in the 1-year questionnaire), the date of start of sexual activity will be equal to the date of the 1-year questionnaire (or visit) minus 6 months.

The date of event will be:

- the date of the detection of the first incident cervical HPV infection (or the date of onset or the first confirmed 6-month cervical HPV infection) during the 48-month follow-up period,

The date of censoring will be:

- the date of Month 48 visit for cervical HPV infections of subjects who attended all visits during the 48-month follow-up period and did not have any cervical HPV infection during this period,
- the date of the last PCR reported at the latest visit for which data are available or the date of the last cytology (if the date is after the date of the last PCR) for cervical HPV infections of subjects who did not attend all visits during the 48-month follow-up period and who did not have any cervical HPV infection throughout their follow-up period (from first to last visit).

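### Section 6.2.7 gives conflicting event rules for women whose sexual activity began less than 6 months before entry and who are HPV positive at Month 0

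*SAP*

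**What the plan says.** - **Population (6.2.7.1).** Women are eligible if "the date of start of sexual activity is either less than 6 months prior to their inclusion in the study or during the follow-up period". The only exclusion based on infection is: "Subjects with cervical HPV infections preceding the start of sexual activity will not be taken into account in the analyses". There is no criterion on Month 0 PCR.
- **Event coding (6.2.7.3).** The lead sentence calls the event the first incident infection, but the category itself reads "1 = First detected cervical infection following the start of sexual activity", with no restriction to detections after enrolment. The section refers the reader to 4.3.1 for the meaning of incident.
- **Event date (6.2.7.4).** The date is "the date of the detection of the first incident cervical HPV infection", during the 48 months of follow-up.
- **Definition of incident (4.3.1).** This is the "new detection of this HPV type (by PCR) at any time point during the follow-up period (i.e. after enrolment in the control arm" of the trial).
- **Censoring (6.2.7.4).** Women who attended every visit are censored at Month 48 if they "did not have any cervical HPV infection during this period". Women who missed visits are censored at their last PCR or cytology if they had no infection between their first and last visit.
- **Month 0 positives elsewhere.** Section 4.2 says some analyses will include them. Sections 6.2.4.1 and 6.2.5.1 each say how they are handled. Section 6.2.7 does not.

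**The concern.** A woman who began sexual activity a few months before entry and is HPV positive at Month 0 already has a detected infection after the start of sexual activity. She meets the event code, but the event-date rule gives that detection no date. Two analysts following this section could assign her very different times, or could disagree on whether she has an event at all.

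These are among the earliest infections that the objective is meant to time. If they are left out, early events are lost and the time to first infection is overstated for the women concerned. This is a secondary objective, reported in a stand-alone report.

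**Working it through.** **1. The plan's own times.** Time is date of event or censoring minus date of start of sexual activity. In Annex 9.4.3, subject #2 started 6 months before Month 0 and is censored at Month 48: 48 − (−6) = 54 months, as printed. Subjects #3 and #5 started at Month 6 and have a detection at Month 24: 24 − 6 = 18 months, as printed. None of the annex examples has a Month 0 detection. (Subject #2 is included at exactly 6 months, although 6.2.7.1 says less than 6.)

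**2. One affected woman.** Let her start *s* months before entry, with 0 ≤ *s* < 6. PCR is scheduled at Months 0, 6, 12, 18, 24, 30, 36 and 48 (Section 3.2).

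- Month 0 counts (6.2.7.3): event at *s*, so 0 to under 6 months.
- Only incident detections count (6.2.7.4 with 4.3.1): event at the earliest at *s* + 6, so 6 to under 12 months.
- No later new detection, and she is nevertheless treated as censorable: censored at *s* + 48, so 48 to under 54 months.

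The differences are (*s* + 6) − *s* = 6 months at least and (*s* + 48) − *s* = 48 months at most. With *s* = 5, the candidate times are 5, 11 or later, and 53 months.

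**3. What the text does with her.**

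- *A new detection follows:* 6.2.7.4 dates the event there, and the Month 0 detection is lost.
- *Negative from Month 6 on:* there is no incident detection. The censoring rule for full attenders could apply if follow-up excludes Month 0. The rule for women with missed visits runs from the first visit, so it does not apply.
- *The Month 0 type stays positive and no other type appears:* there is no new detection, yet she is not free of infection during follow-up. She has neither an event date nor a censoring date.

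**4. Illustrative size.** The SAP gives neither the number of pre-entry starters nor their Month 0 positivity, so every input here is assumed. A share *q* of the analysis set started uniformly over the 6 months before entry. The rest started uniformly over Months 0 to 36. A share *p* of pre-entry starters is positive at Month 0. The later infection hazard is 0.02 per month, the same for all women, and detection occurs at the PCR visits. There were 4,000 simulated women and one run per row. Entries are Kaplan-Meier cumulative incidence at 12 months from the start of sexual activity.

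| *q* | *p* | Month 0 counted | ignored | women excluded | counted − ignored (points) |
|---|---|---|---|---|---|
| 10% | 5% | 15.4% | 14.9% | 14.9% | 0.5 |
| 10% | 15% | 15.3% | 14.1% | 14.1% | 1.2 |
| 10% | 25% | 16.8% | 14.5% | 14.4% | 2.3 |
| 30% | 5% | 15.0% | 13.6% | 13.6% | 1.4 |
| 30% | 15% | 16.9% | 12.8% | 13.0% | 4.1 |
| 30% | 25% | 20.4% | 13.7% | 13.8% | 6.7 |
| 50% | 5% | 15.8% | 13.6% | 13.7% | 2.2 |
| 50% | 15% | 18.6% | 12.7% | 12.4% | 5.9 |
| 50% | 25% | 24.4% | 13.8% | 13.7% | 10.6 |

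As a rough check, the gap should be near *q* × *p* × (1 − incidence when ignored). The first row gives 0.10 × 0.05 × (1 − 0.149) = 0.4 points, and the last gives 0.50 × 0.25 × (1 − 0.138) = 10.8 points. Both agree with the table within simulation noise.

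**The case against.** The strongest defence is that the plan never says these women are followed as uninfected. A reader might infer it from the incident definition, but the censoring rules ask for no infection at all, and one of them expressly starts at the first visit. That objection stands. Following such a woman as uninfected is one reading, open mainly for full attenders who are negative from Month 6.

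Other readings would avoid the problem. The event code in 6.2.7.3 can be read to count Month 0. Section 4.2 says only that some analyses include Month 0 positives, so exclusion could be intended. The flowcharts in Annexes 9.2 and 9.3.4 are not visible in the text available and might carry a rule. These points limit what can be said about intent. They do not reconcile the written event code with the written event date.

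Four further inferences are tempting but not supported:

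- *She stays event-free until a different type appears.* Section 6.2.7.3 treats same-type infections separated by clearance as distinct, so re-detection of the same type can count. No firm share of these women can be said never to have a later event.
- *A first persistent infection would precede the first infection.* Section 4.3.1 dates persistence from the first positive sample with no enrolment limit, so this can happen on one reading. But the follow-up restriction in 6.2.7.4 may cover both event dates.
- *Effects of determinants are biased toward no effect.* This is plausible, but no covariate effect was calculated.
- *The distortion among pre-entry starters applies to the whole analysis.* The set also includes women who started during follow-up, who are unaffected. Women who started earlier before entry are excluded (Annex 9.4.3, subject #1).

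**Conclusion.** The concern holds as a contradiction together with a missing Month 0 rule. For pre-entry starters who are positive at Month 0, the event code and the event date disagree, and the censoring rules do not settle the matter. Applied as written, the event-date rule times a later detection as the first infection at least 6 months late, assuming visits on schedule. A woman with no later detection has no clear outcome.

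The effect on the whole analysis cannot be determined from the SAP. The illustration gives about 0.5 to 11 percentage points at 12 months, resting on the assumed shares, the constant hazard and the reading that ignores Month 0. A correction is warranted, in proportion to a subset of one secondary objective.

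**What to change.** Align 4.3.1, 6.2.7.1, 6.2.7.3 and 6.2.7.4 on one explicit rule for women who started before entry and are positive at Month 0. Either of two rules would do:

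- **Count the Month 0 detection as the first infection.** Its true time lies between the start of sexual activity and Month 0. Treat it as interval- or left-censored, or date it at Month 0 and report that time as an upper bound.
- **Exclude these women explicitly.** The remaining pre-entry starters should then enter the risk set at Month 0, since they were selected as negative at that visit. This removes the contradiction but does not recover the early infections: in the table, exclusion gives almost the same incidence as ignoring them.

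State the handling of a missing Month 0 PCR as well. Apply the same origin rule to the first persistent infection, reword the censoring conditions to match, and add a Month 0 positive example to Annex 9.4.3. Report a sensitivity analysis restricted to women whose sexual activity started during follow-up, in whom this problem cannot arise.

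The cost is SAP wording and one extra analysis, since the Month 0 PCR results are already collected. The downside is that event times dated at Month 0 are upper bounds, or, under exclusion, that some subjects are lost, in a number the SAP does not give.

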### 3.2 Study procedures resulting in data to be used for analyses

- Blood samples for all subjects were drawn at Months 0, 7 and 24 and in a subset of subjects from selected study sites.
- Gynecological examinations were performed at Months 0, 12, 24, 36 and 48.
- Cervical liquid-based cytology samples were collected at Months 0, 6, 12, 18, 24, 30, 36 and 48:
  - HPV DNA typing by PCR was performed on cervical liquid-based cytology samples at Months 0, 6, 12, 18, 24, 30, 36 and 48,
  - Cytopathological examinations were performed on liquid-based cytology samples to detect abnormal cells at Months 0, 12, 24, 36 and 48 in all subjects,
  - Screening for *Chlamydia trachomatis* and *Neisseria gonorrhoeae* on liquid-based cytology samples at Months 0, 12, 24, 36 and 48.

Note: As of Protocol Amendment 2, screening for *Neisseria gonorrhoeae* was done only if considered appropriate by the investigator.

- Colposcopic referral according to appropriate clinical management algorithms. A central laboratory processed and interpreted results from liquid-based cytology and histology samples. All CIN endpoints were confirmed by an expert histopathology review panel that was blinded to vaccine status, HPV DNA status before biopsy and cytology reports. An Endpoint Committee was responsible for reviewing all available clinical and laboratory data prior to study unblinding by the external statistician to make final case assignments for all subjects assumed to meet criteria for primary and secondary efficacy endpoints.

- Behavioral questionnaire completed by interview for all subjects at Months 1, 12, 24, 36 and 48. The behavioral questionnaire (self-administered) collected specific socio-demographic and behavioral data concerning determinants that are recognized to predispose subjects to cervical HPV infection or are recognized co-factors for cervical carcinogenesis. The baseline questionnaire assessed at Month 1 collected data which occurred during past history and during the previous year. Questionnaires assessed at Month 12, 24, 36 and 48 collected data assessed during the previous year.

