## 9.2 Flowchart of cervical HPV infection endpoint determination

[figure not shown]

The following rules will be applied for the determination of cervical HPV infections in case a HPV type is detected at the last known visit of a patient and was not detected at the previous visits:

| Visit v  | Visit v+1 | Visit v+2             | Rule for the determination of cervical HPV infections and clearance             |
|----------|-----------|-----------------------|---------------------------------------------------------------------------------|
| No HPV-X | No HPV-X  | HPV-X
(last visit) | Other cervical HPV infection at Visit v+2
No clearance of HPV-X at visit v+2 |

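### Time to first 6-month persistent infection is censored at Month 48, although on the stated PCR schedule no onset after Month 36 can be confirmed

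*SAP*

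**What the plan says.** The relevant rules are spread over several sections of the SAP.

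- **Sampling (3.2):** "HPV DNA typing by PCR was performed on cervical liquid-based cytology samples at Months 0, 6, 12, 18, 24, 30, 36 and 48". The visit list in section 3.1 has no Month 42 visit either.
- **Persistence (4.3.1):** a run of positives for one type, "not interrupted by negative samples, such that the total range is more than 5 months" (over 150 days). "The start of the persistent cervical HPV infection is defined as the date of the first positive sample in the sequence".
- **Infections first seen at the last visit:** section 4.3.1 puts them in a residual class, "cervical HPV infections detected at the last visit and for which it is not possible to determine if they are transient or persistent". The rule table in Annex 9.2 does the same: "Other cervical HPV infection at Visit v+2".
- **Event date (6.2.7.4):** for the persistent endpoint, "the date of onset or the first confirmed 6-month cervical HPV infection". This is the onset, not the confirming sample.
- **Censoring date (6.2.7.4):** for completers, "the date of Month 48 visit for cervical HPV infections of subjects who attended all visits during the 48-month follow-up period". The sentence goes on to limit this to women with no cervical HPV infection in that period. Non-completers are censored at the last PCR, or at the last cytology if that is later. No separate rule is given for the persistent endpoint.
- **Who enters (6.2.7.1):** women whose sexual activity began "either less than 6 months prior to their inclusion in the study or during the follow-up period", so debut after Month 36 is admitted.

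**The concern.** A woman should count as at risk only while an event could be recorded for her. Under these rules a completer stays in the risk set for 12 months after the last visit at which a persistent infection can begin and still be confirmed. A woman who starts sexual activity after Month 36 is in the risk set throughout with no possibility of an event.

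Three results are exposed: the event density (section 6.2.3.1, events over person-months at risk), the Kaplan-Meier curve, and the Cox hazard ratios for any determinant related to the date of debut. The empty 12 months are a larger fraction of follow-up the later debut occurs, and age at first intercourse is a listed covariate for this endpoint (Annex 9.5.4).

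**Working it through.** **1. The plan's own figure.** Annex 9.4.3, subject #2: debut 6 months before Month 0, no infection, censored at 48 − (−6) = 54 months, as printed. Time in which a confirmable onset could occur: 36 − (−6) = 42 months. Empty: 54 − 42 = 12 months.

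**2. Latest confirmable onset.** Each PCR visit from Month 0 to Month 36 has a later scheduled PCR more than 150 days away (for Month 36, it is Month 48). Month 48 has none.

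**3. Empty share by debut month s for a completer** = (48 − max(s, 36)) / (48 − s):

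| s | Empty / follow-up (months) | Share |
|---|---|---|
| −6 | 12/54 | 22% |
| 0 | 12/48 | 25% |
| 12 | 12/36 | 33% |
| 18 | 12/30 | 40% |
| 24 | 12/24 | 50% |
| 30 | 12/18 | 67% |
| 36 or later | all | 100% |

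**4. Pooled share.** The SAP gives no distribution of debut dates. The spreads below are assumptions: uniform, no drop-out, events ignored.

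| Debut uniform over Months | Mean empty / mean follow-up (months) | Share |
|---|---|---|
| −6 to 0 | 12/51 | 23.5% |
| −6 to 12 | 12/45 | 26.7% |
| −6 to 24 | 12/39 | 30.8% |
| −6 to 36 | 12/33 | 36.4% |
| −6 to 48 | 10.67/27 | 39.5% |
| 0 to 48 | 10.5/24 | 43.8% |

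For −6 to 48, the empty time is (42/54)×12 + (12/54)×6 = 10.67 months, and 12/54 = 22% of women cannot have an event. For 0 to 48, it is (36/48)×12 + (12/48)×6 = 10.5 months.

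**5. Effect on the rate.** This assumes a constant hazard of 0.002 to 0.02 per month and keeps transient-only women as non-events. The ratio of observed to true rate is 0.61 to 0.62 for debut over −6 to 48, and 0.77 to 0.83 for debut over −6 to 0.

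**6. Effect on the Kaplan-Meier estimate** (assumed hazard 0.01 per month, onset times treated as exact):

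| Debut | Time since debut | True | Month 48 censoring | Month 36 censoring |
|---|---|---|---|---|
| −6 to 48 | 24 months | 21.3% | 15.2% | 21.1% |
| −6 to 48 | 36 months | 30.2% | 20.0% | 30.2% |
| −6 to 12 | 24 months | 21.3% | 21.4% | 21.4% |
| −6 to 12 | 36 months | 30.2% | 27.4% | 30.3% |

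If debut is early, the curve is unaffected until time since debut reaches past Month 36. The bias in the curve therefore depends more on the debut distribution than the bias in the rate does.

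**7. Effect on a covariate.** A simulation with no true effect used hazard 0.01, assumed entry ages of 15–18 or 15–20, and debut uniform over −6 to 24 or −6 to 48. The hazard ratio for first intercourse at 18 or older was 0.57 to 0.89 under Month 48 censoring and 1.06 to 1.29 under Month 36 censoring. The remaining departure from 1 comes from dating infections at visits, not from the censoring rule. It was smaller on the log scale in every scenario.

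**8. Early leavers.** PCR gaps up to Month 36 are 6 months, so the interval before the last PCR is empty in the same way but usually half as long as for completers.

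**The case against.** **Size.** A reader might infer that about 40% of follow-up is empty. The SAP does not support this as a fact. It holds if debut is spread evenly over Months −6 to 48, or for a woman whose debut is at Month 18. Only the 22% minimum for a completer follows from the SAP alone.

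**Direction.** A reader might infer that the rate is certainly understated. That depends on who is in the denominator, and the SAP disagrees with itself. In section 6.2.7.3, subject B has only transient infections and is included with persistent event 0. In Annex 9.4.3, subjects #3 and #5 also have only transient infections and are left out of the persistent analysis. The censoring text in 6.2.7.4 covers only women with no infection, so transient-only and last-visit infections have no written censoring date. If such women were dropped, simulation (persistent hazard 0.005 to 0.02 per month, transient hazard 0.5 to 3 times that, debut over −6 to 48) put the ratio of observed to true rate anywhere from 0.69 to 1.95. The objection stands: the downward bias is established only under the section 6.2.7.3 reading.

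**Month 42.** The Annex 9.4 tables have a Month 42 column, and subject #5 in 9.4.3 has a type detected there. With a real Month 42 sample the empty period would be 6 months, and the uniform −6 to 48 share would be ((48/54)×6 + (6/54)×3)/27 = 5.67/27 = 21%. Sections 3.1 and 3.2 list no such visit, and the annex tables are illustrations, so the 12-month figure is the better supported one.

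**Cytology.** Scheduled cytology uses the same samples as PCR, so moving censoring to a later cytology date will often change little. No size can be given.

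**Importance.** This is one secondary endpoint in a stand-alone report. The primary endpoint and first incident infection are not affected.

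**Conclusion.** The concern holds in limited form. On the PCR schedule in sections 3.1 and 3.2, the single censoring rule counts Months 36 to 48 as time at risk for an event that cannot be recorded then, and it admits women who can never have the event. The empty share is at least 22% for any completer and about 23% to 44% pooled under the debut spreads tried.

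If transient-only women are kept as non-events, the event density is biased downward. The cumulative probability is biased downward at times since debut that reach past Month 36. Determinants tied to late debut can look falsely protective. If those women are dropped, the direction is not determined.

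The SAP already reasons along these lines elsewhere: section 6.2.6.4 excludes last-visit infections from the optional Cox model for clearance. This should be fixed before the endpoint is analysed, but it does not threaten the main results.

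**What to change.** In section 6.2.7.4, for the first-persistent-infection endpoint only:

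- Censor each woman without a persistent event at her last PCR that is followed by another PCR more than 150 days later (Month 36 for completers). Apply this also to women with only transient or last-visit infections. Annex subject #2 would then be censored at 42 months, not 54.
- Exclude women whose sexual activity starts after that date. They carry no information on this endpoint.
- Do not extend censoring to a cytology date.
- Leave the rule for first incident infection at the last PCR.

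Reconcile section 6.2.7.3 (subject B), the censoring text in 6.2.7.4, and Annex 9.4.3 (subjects #3 and #5), so that the denominator is defined once. Correct or explain the Month 42 column in Annex 9.4.

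State one remaining limit. An onset at Month 36 is confirmed only by a positive 12 months later, so infections that last 6 months but clear before Month 48 are still missed.

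The cost is a sentence or two, one derived date and corrected examples. No new data are needed.

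### Time to first infection: event-free women may be censored at a cytology or Month 48 visit date without a PCR result, although only PCR can show the event

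*SAP*

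**What the plan says.** Section 6.2.7.4 gives two censoring rules for women without an infection. Those who attended everything are censored at "the date of Month 48 visit for cervical HPV infections of subjects who attended all visits during the 48-month follow-up period"; the rule does not ask for a PCR result at that visit. The others are censored at the last reported PCR, "or the date of the last cytology (if the date is after the date of the last PCR").

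Section 4.3.1 defines both events by PCR. An incident infection is "the new detection of this HPV type (by PCR) at any time point during the follow-up period". A 6-month persistent infection "is defined as the detection of the same HPV type (by PCR) in cervical samples at two consecutive evaluations over approximately a 6-month interval", with positives spanning more than 150 days.

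Section 3.2 gives the schedules: "HPV DNA typing by PCR was performed on cervical liquid-based cytology samples at Months 0, 6, 12, 18, 24, 30, 36 and 48", and "Cytopathological examinations were performed on liquid-based cytology samples to detect abnormal cells at Months 0, 12, 24, 36 and 48 in all subjects".

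**The concern.** Cytology looks for abnormal cells and does not type HPV. The cytology clause applies only when the cytology falls after the last PCR, so every day it adds is a day on which the event could not be observed. The Month 48 rule does the same for a woman who attended that visit but has no usable PCR result from it.

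No other section resets the date. Section 4.5.1 foresees a missing HPV type at the last visit and gives rules for infection class and clearance, but none for censoring. Section 4.5.2 drops subjects whose endpoint measure is missing. It does not say that a woman with earlier negative PCRs and a missing last one is such a case.

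The extra months enter the person-month denominator of the density estimates in section 6.2.3.1. They also keep women in Kaplan-Meier and Cox risk sets in which they cannot fail. The rate is therefore pushed down. If missing PCR results differed between determinant groups, the comparisons in the objective would shift too.

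**Working it through.** **Inputs from the SAP.** PCR at Months 0, 6, 12, 18, 24, 30, 36 and 48; cytology at Months 0, 12, 24, 36 and 48 (section 3.2); the censoring rules of 6.2.7.4; the worked example in Annex 9.4.3.

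**Inputs assumed, because the SAP does not give them.** The share of women affected, mean follow-up, and the rate of first detection.

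1. *The plan's own figure.* Example subject #2 in Annex 9.4.3 began sexual activity 6 months before Month 0 and had no infection through Month 48. Censored time = 48 − (−6) = 54 months, as stated.

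2. *The same woman without a Month 48 PCR result.* If her last valid PCR is at Month 36, the time in which an event could be seen is 36 − (−6) = 42 months. The SAP rule still gives 54. The excess is 12 months, or 12/42 = 29% for this woman.

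3. *When an excess can arise.* Every scheduled cytology month is also a PCR month. With a PCR result on the last sample, the two rules agree and the excess is 0. If only the last PCR is missing, the scheduled gaps are 24 − 18 = 6, 36 − 30 = 6 and 48 − 36 = 12 months.

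4. *Person-time.* Inflation = share affected × extra months ÷ mean follow-up, with 30 months assumed:
   - 2% and 6 months: 0.02 × 6/30 = 0.4%
   - 5% and 12 months: 0.05 × 12/30 = 2.0%
   - 10% and 12 months: 0.10 × 12/30 = 4.0%

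   The rate is understated by nearly the same amount: 1 − 1/1.004 = 0.4%, and 1 − 1/1.04 = 3.8%.

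5. *Check with a constant detection rate.* Let λ be the yearly rate, L the years to the last valid PCR, g the gap in years, and f the share of event-free women with the gap. Then S = exp(−λL), true person-time is (1 − S)/λ, the SAP rule gives (1 − S)/λ + f·S·g, and estimated rate ÷ true rate is the first divided by the second. For λ = 0.2, L = 3, g = 1, f = 0.10: S = 0.549, person-time is 2.256, the SAP rule gives 2.256 + 0.055 = 2.311, and the ratio is 0.976, so the rate is 2.4% too low. Over λ = 0.1-0.3 and f = 2-20%, the rate is 0.4-5.4% too low for a 12-month gap after 3 years, and 0.3-5.8% too low for a 6-month gap after 1.5 or 2.5 years.

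6. *Late Kaplan-Meier curve.* Simplify by giving all women a common time origin and counting Month 48 detections before Month 48 censorings. If a share m of those still at risk has no Month 48 PCR, the Month 36-48 detection probability shrinks by (1 − m). At λ = 0.2 and m = 10%: true 1 − exp(−0.2) = 0.181; estimated 0.181 × 0.9 = 0.163.

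7. *Group comparisons.* With λ = 0.2, L = 3, g = 1, no gap in one group and f = 20% in the other, a true rate ratio of 1 becomes 2.256/(2.256 + 0.110) = 0.95. The SAP gives no sign that missing PCR results differ in this way.

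**The case against.** The strongest reply is that the gap is rare by design. PCR and scheduled cytology share the same samples and visits, and Month 48 is by schedule the last PCR visit of a full attender. This stands, and it limits the point to missing or invalid last PCRs and to cytology taken off schedule.

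A reader might infer that a woman is censored at Month 48 whatever her PCR shows there. The text does not support that: the rule covers only women without any infection, and a positive Month 48 PCR is an event for first infection. The gap is confined to women with no Month 48 result. Nor should 0.4-4% be read as an estimate for this trial, since the SAP supports neither the 2-10% nor the 30 months. The upper end needs a 12-month gap for all of the 10%.

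Other timing error in 6.2.7.4 may be larger. Start of sexual activity is birthdate plus reported age (up to about 12 months' error if age is in whole years, which is an assumption) or is placed by halving an interval. Detection itself is known only to within 6 to 12 months. This is fair on proportion, but those errors do not cancel this one.

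The clause resembles the lesion rules in 6.2.4.4 and 6.2.5.4, which add the last biopsy. That it was carried over from them is conjecture, and the point does not depend on it.

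**Conclusion.** The point holds and is minor. Followed as written, 6.2.7.4 can count 6 or 12 months per affected woman in which neither event could be shown, and the bias in the first-infection rate is downward. The size depends on a share that the SAP does not state: about 0.4-4% extra person-time under the assumptions above, and zero if no last PCR is missing. Bias in determinant effects would also require missing PCR results to differ by group. The analysis serves secondary objectives in a stand-alone report; the primary endpoint is untouched.

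A reader might infer that censoring at the last valid PCR settles both endpoints. It does so only for first infection. A first positive at the last valid PCR cannot be confirmed as persistent, because section 4.3.1 requires positives more than 150 days apart. The persistent endpoint needs an earlier date.

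**What to change.** In section 6.2.7.4, delete the cytology clause and use one rule for all attendance patterns:

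- *First infection:* censor women without the event at their last sample with a valid HPV PCR result.
- *First 6-month persistent infection:* censor at the last valid PCR sample from which persistence could still be confirmed, that is, one followed by a further valid PCR more than 150 days later.

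Report how many women have a later visit or cytology without a PCR result, so that the effect can be judged. The change takes a sentence or two and no new data. Its cost is slightly shorter censoring times, more so for the persistent endpoint.
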